# Group-based PFMT programme for preventing and/or treating UI in pregnant women: protocol of a randomized controlled feasibility study

**DOI:** 10.1186/s40814-023-01410-2

**Published:** 2023-10-31

**Keywords:** Group-based intervention, Pelvic floor muscle training, Urinary incontinence, Pregnant women

## Abstract

**Background:**

Urinary incontinence (UI) is a prevalent health problem in women worldwide. Many women experience UI during pregnancy. The National Institute for Health and Care Excellence (NICE) recommended pelvic floor muscle training (PFMT) as the first-line conservative treatment for UI. However, it is not widely implemented due to the limited number of healthcare trainers. Group-based PFMT has been used with older women and a limited number of maternity studies. But the effectiveness of the group-based PFMT needs to be investigated because the overall quality of the studies is low. Therefore, this study aims to assess the feasibility of delivering a group-based PFMT programme for pregnant women in Nanjing city.

**Methods:**

This feasibility study will be conducted in Nanjing Maternity and Child Health Care Hospital in China, using a mixed methods design to investigate the feasibility and acceptability of delivering group-based PFMT to pregnant women. Pregnant women with or without the symptoms of UI will be included. This study aims to recruit 48 pregnant women with 24 in each arm. Participants will receive either the group-based PFMT delivered by a midwife or usual antenatal care which includes only verbal instruction on PFMT. The study will assess the completion rates, acceptability of outcome measures, recruitment and retention rate and calculate an appropriate sample size for a future study.

**Discussion:**

The results of this study will inform the design and implementation of a definitive randomized clinical trial to explore the effectiveness of the intervention.

**Trial registration:**

ClinicalTrials.gov, NCT05242809.

**Supplementary Information:**

The online version contains supplementary material available at 10.1186/s40814-023-01410-2.

## Background

Urinary incontinence (UI), one of the most prevalent health problems in women worldwide, is defined as a complaint of involuntary loss of urine [1]. Many women experience UI during pregnancy, and the prevalence of UI peaks in the third trimester [2]. Physiological changes occur during pregnancy including increased abdominal pressure and progesterone levels. Along with injury to pelvic floor muscles during vaginal delivery, the strength and endurance of pelvic floor muscles may be damaged which make women more susceptible to UI [3, 4].

The National Institute for Health and Care Excellence (NICE) recommended conservative treatment for the management of UI, for example, lifestyle interventions, physical therapies including pelvic floor muscle training and electrical stimulation, behavioural therapies and neurostimulation [5]. In addition, researchers explored other approaches to provide more conservative therapeutic options for UI, for example, vaginal cones [6], pelvic floor electromyography biofeedback [7] and magnetic stimulation [8] although these options have not been widely used and recommended.

Individualized pelvic floor muscle training (PFMT) is recommended as a first-line conservative treatment for stress urinary incontinence (SUI) and any type of UI in the clinical practice guidelines [9]. However, PFMT is not implemented in many countries often due to a limited number of suitably skilled health professionals [10–12]. In order to provide PFMT to more women and overcome the human resource barriers, there is a need to explore methods of implementing PFMT at scale.

Recent systematic reviews showed that group-based PFMT was effective in preventing and treating UI in pregnant women [13, 14]. Group-based approaches have been employed within health promotion for many years and found to be an economical way to facilitate behaviour modification [15]. In addition, group-based interventions are reported to foster peer support, reduce stigma and isolation feelings and encourage active self-management [16]. It was reported that group-based training has a positive impact on self-management which could facilitate adherence to PFMT and support women to undertake the exercise in the long term [17]. However, a limited number of studies were found to assess the effectiveness of group-based PFMT in pregnant women [13]. In addition, the overall quality of the included studies was assessed to be low based on the Grading of Recommendations, Assessment, Development and Evaluations (GRADE) [13].

Well-designed randomized controlled trials are needed to provide evidence of the effectiveness of group-based PFMT in pregnant women. According to the Medical Research Council (MRC) framework, feasibility or pilot studies should be conducted before a full-scale randomized controlled trial to investigate the acceptability of an intervention, estimate the likely rates of recruitment and retention and calculate appropriate sample sizes [18]. In addition, sample characteristics, adherence and identification of effective recruitment approaches can be assessed through a feasibility study. Feasibility studies can help to avoid human and financial research waste in a large RCT [19]. Therefore, this paper describes the protocol for the feasibility testing of a group-based PFMT programme in pregnant women in Nanjing city in China before evaluating the effectiveness within a fully powered RCT.

## Research question

Is it feasible to deliver a group-based PFMT programme to pregnant women in Nanjing city in China?

## Method

### Aims and objectives

This study aims to test the feasibility and acceptability of the intervention in preparation for a full-scale randomized controlled trial. The objectives of the study are as follows:To explore the feasibility and acceptability of the group PFMT intervention in pregnant women in Nanjing city in ChinaTo estimate the recruitment and retention rates for a group-based PFMT supervision programmeTo assess the attendance and adherence within the supervised PFMT programmeTo assess the acceptability of proposed outcome measuresTo conduct a process evaluation through post-intervention interviews with the participants and the midwife implementer to consider intervention fidelity and refine the programme for future trial

### Study design

This single-centred, three-phased study uses a mixed methods research design guided by the MRC [18] and behaviour change wheel (BCW) frameworks [20]. The use of these validated frameworks within the feasibility study will be published separately in a co-design paper. This trial will comprise a two-arm feasibility RCT, in which participants will be randomly allocated to either group-based PFMT or usual antenatal care. Participants will be assessed at three time points during the study: baseline (24 gestational weeks), post-intervention (approximately 36 gestational weeks) and follow-up assessment (42 days after delivery). This study has been approved by the ethics committees of King’s College London (LRS/DP-21/22–26,714) and Nanjing Maternity and Child Health Care Hospital (2021-KY-084) and has been registered with ClinicalTrials.gov under NCT05242809. This study has been designed following the Standard Protocol Items: Recommendations for Interventional Trials (SPIRIT) [21] and reported according to the Consolidated Standards of Reporting Trials (CONSORT) extension for pilot and feasibility trials statement [22]. The SPIRIT checklist is presented as the Additional file 4: Table S1. The study flow diagram is presented in Fig. 1.

**Fig. 1 Fig1:**
[figure not shown]
Flow chart of the feasibility study

The study comprises three phases: co-design of the group-based PFMT programme (phase 1), feasibility testing of the group-based PFMT programme (phase 2) and a process evaluation (phase 3). The process of the co-design of the group-based PFMT programme is in preparation for publication elsewhere, and the protocol for phases 2 and 3 is reported in this paper.

### Setting and sampling

The feasibility of two-arm RCT will be conducted in the antenatal clinic at Nanjing Maternity and Child Health Care Hospital in China. It is one of the biggest maternity hospitals in Nanjing city, where 50 to 80 women at around 19–20 gestational weeks attend antenatal care appointments each day following their referral to the hospital for their maternity care. Nanjing city is the capital city of Jiangsu province and is a well-developed city in China [23]. The prevalence of UI in pregnant women in this city was reported to be 37.8% in 2020 [24]. The selection of enrollment at 24 gestational weeks is based on the discussion in workshops with stakeholders and evidence. Pregnant women in their 19–20 gestational weeks need to be referred to a general hospital or an obstetric hospital from community hospitals in China. It is not possible to provide the group-based PFMT programme to the same group of women for consecutive 3 months until they are referred to a general hospital or an obstetric hospital. In consideration of the feasibility of this study, the stakeholders discussed not increasing the number of pregnant women’s visits to the hospital. Therefore, this study started recruiting pregnant women on their first visit to the obstetric hospital and obtaining their consent on participating in the group-based PFMT programme, then started providing face-to-face supervision on their next antenatal check (around 24 gestational weeks) and support them to perform this exercise at least 3 months in their pregnancy which is recommended by the NICE.

### Sample size

As this is a feasibility study, formal sample size calculation has not been performed. The sample size for a feasibility study needs to meet a balance between not being too large, which may cause a burden on health professionals and participants, and also not being too small as the consent rate, attrition and sample size for a large-scale RCT need to be calculated. Based on the recommendation from the National Institute for Health Research [25], an overall sample size of 30 or greater was considered sufficient for a feasibility study. In addition, a sample size between 24 and 50 is sufficient to calculate a standard deviation of an outcome, which can then be used for a formal calculation for a full-scale RCT [26, 27]. A study by Whitehead et al. [28] developed a method for determining the best approach to calculate the required sample size for a pilot trial and found that for studies where standardized differences are large, to achieve 90% power in the main trial, the required sample size for each arm is 10. For women receiving nonsurgical therapies for incontinence, reductions of four to six points in the International Consultation on Incontinence Questionnaire-Urinary Incontinence Short Form (ICIQ-UI SF) are needed to show clinically meaningful [29]. Two further studies consider the attrition rates in group-based pelvic floor muscle training in pregnant women or postpartum women range from 8.57 to 53.33% [30, 31]. Therefore, this study aims to include a sample size of 48 participants with 24 in each arm.

### Eligibility criteria

This study will target pregnant women meeting the inclusion criteria attending the antenatal clinic in Nanjing Maternity and Child Health Care Hospital without considering whether they have symptoms of UI during pregnancy.

The following are the inclusion criteria:Nulliparous women who are aged 18 years and olderGestational ages of 19–24 weeksWith or without the symptoms of UISingleton foetusCapable of giving valid informed consent

The following are the exclusion criteria:Women with pregnancy complications or urinary tract infectionWomen with pre-existing UI symptoms before pregnancyWomen at high risk of preterm labourWomen with a history of previous urogenital surgery or diseases that may interfere with pelvic floor muscle strength, for example, pelvic organ prolapse, neurological disorders and diabetes

### Recruitment, consent, assessments, randomization and allocation concealment

The principal researcher will provide details of the study to the midwives and nurses who run the Nanjing Maternity and Child Health Care Hospital antenatal clinics. The midwives and nurses will be responsible for giving information about this study to the women. The midwives and nurses will screen potential participants based on the inclusion criteria to determine whether they are eligible to take part in the study when they attend the antenatal clinics at around 19–20 gestational weeks. If the participants are eligible to take part in the study, the midwives and nurses will provide participants with an information sheet. The midwives and nurses will be trained before speaking to women to assess eligibility for the study, and the midwives and nurses will inform the potential participants that the questions are asked only for assessing whether they are eligible for the study; this information will not be recorded in their medical records. Potential participants will be informed that choosing not to take part in or withdrawing from the study will not affect the care, treatment or service they receive in any way. They may also choose not to take part in the study or withdraw from the study at any time without giving a reason.

Potential participants will not need to tell the midwives and nurses whether they want to take part in the study at the time. They will take the information sheet home to consider whether to take part in the study or not before they attend their next antenatal clinic appointment at around 23–24 gestational weeks. If the participants are willing to participate in the study, they will be asked to contact the principal researcher using the contact information on the information sheet before their next antenatal appointment.

Any woman who expresses interest will be telephoned by the principal researcher. The principal researcher will ensure all the participants understand the detailed study information they have been given. They can also discuss the study and any questions they might have with the principal researcher. Following the call, they will still have time to consider whether to participate in the study before their 24 gestational week antenatal appointment. If they agree to participate in the programme, they will be scheduled a date before 24 gestational weeks to meet the principal researcher, and written informed consent will be obtained. If the participants withdraw their interest before providing consent, recruitment will continue until there are enough potential participants. The time for recruitment and randomization will be extended to ensure enough participants are recruited for the study. After the participants have signed the consent form, they will meet the research midwife in another office in the hospital and complete the baseline data.

The participants will be randomly allocated to the usual antenatal care or group-based PFMT programme by using a computerized block randomization programme which is generated by the principal researcher (the size of the block is 16). Allocation will be concealed by using sealed opaque envelopes. The envelope will be offered to the participants in sequence by the midwife. They will complete the baseline assessment after randomization. The participants who are randomized to the group-based supervision group will then be scheduled a date by the midwife for the first group training session. The flowchart of the feasibility study and the flow for participants is presented in Additional file 2. According to the inclusion and exclusion criteria, 75% of the pregnant women are estimated to be eligible [32, 33]. Therefore, the recruitment is expected to be completed within 3 months, and the screening of the pregnant women will stop when 48 participants have been recruited. No reimbursement was provided for women consenting to participate or continue participating in this study.

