### Blinding

It is not possible for the midwife delivering the intervention to be blinded to the pregnant women in the intervention groups or the usual antenatal care group. Also, the principal researcher will not be blinded to the participants to be invited in the interviews post-intervention. However, the principal researcher, who will be conducting baseline and follow-up data analysis, will be blinded to the allocation when analysing the feasibility data.

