### Interventions

The participants in the intervention group will receive PFMT supervision in groups of eight women. The intervention will include verbal instruction on PFMT, the use of models and pictures of the pelvic floor to help women identify their pelvic floor muscles and then guide them on how to contract the pelvic floor muscles correctly. The content of this PFMT programme was adapted from a published protocol [34] and co-designed with stakeholders to suit the needs of a different population (pregnant women) and setting (Nanjing city) as recommended by the MRC framework [18]. The stages in co-designing the group-based PFMT programme are described in Additional file 2. In brief, the exercise includes three repetitions with 2-min rests between each repetition. One repetition comprised eight contractions with each held for 6 s, followed by three or four fast contractions. Learning and practising the exercise will be supervised in the group sessions and will be required to be repeated twice per day at home between group sessions.

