All the group-based training sessions in the programme will be provided by one midwife to ensure consistency. The midwife will be trained beforehand by the principal researcher about the PFMT programme. The participants will be required to meet the midwife for group supervision once a month on the day of their regular antenatal check for consecutive four consecutive months (approximately 24 gestational weeks, 28 gestational weeks, 32 gestational weeks and 36 gestational weeks). The group supervision sessions will last for about 45 min which include attendance registration and progress review (5 min), education on the causes of UI and PFMT (10 min), skills training in sitting and standing positions (20 min), discussion on what is taught (8 min) and reminder about the next session (2 min). The registration of attendance and the training diary which will be provided to the participants after each session will be monitored to record adherence to the programme. Women who attend at least 75% of the supervision sessions will be considered as adherent. Motivation to maintain PFMT will be emphasized by the midwife and supported by WeChat groups which will be limited to the eight pregnant women in the group session. A reminder to practise PFMT as well as the audio instructions on doing PFMT will be sent automatically in the WeChat group twice a day. In addition, leaflets on PFMT, training diaries and stickers which motivate the participants to undertake PFMT will be provided. The PFMT leaflets and training diary were provided as Additional file 3. One day before the next session, a reminder of the session date will be sent to the WeChat group. The participants will be encouraged to discuss any topics related to PFMT and UI in the WeChat group to facilitate peer support. The midwife and the principal researcher will adopt administrative roles and monitor the WeChat groups but will not answer questions or participate in discussions. Any problems which the pregnant women encountered during the exercises will be addressed during face-to-face supervision. There will be ground rules set for the groups, for example, the women in the groups need to keep the information confidential within the group and treat each woman in the group with respect. If any women break the ground rules or discuss information in the WeChat group that is unsafe, the principal researcher will remind the women about the ground rules and correct any information that is dangerous. During the development of this study, the barriers identified from the systematic review [13], survey [24] and discussion with stakeholders, such as time commitment, forget to continue PFMT were mapped to the COM-B model and explored in a separate study. For reasons of equipoise, women in the comparator group will be offered the group-based PFMT intervention at the end of the study if they wish.

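### A single fixed block of 16, matching one training group of eight, makes about 5 of 48 allocations certain to anyone who counts; vary and withhold the block sizes

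*Protocol article*

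**What the plan says.** All references are to the protocol article.

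- **Sample size:** "this study aims to include a sample size of 48 participants with 24 in each arm".
- **Recruitment, consent, assessments, randomization and allocation concealment:** the list comes from a "computerized block randomization programme which is generated by the principal researcher (the size of the block is 16". No other block size is given, and nothing says that the size is kept from staff. On concealment: "Allocation will be concealed by using sealed opaque envelopes". On delivery: "The envelope will be offered to the participants in sequence by the midwife". The midwife then books intervention women for their first session. Before that, the principal researcher telephones interested women, and if they agree "they will be scheduled a date before 24 gestational weeks to meet the principal researcher, and written informed consent will be obtained".
- **Interventions:** "The participants in the intervention group will receive PFMT supervision in groups of eight women". Each WeChat group is limited to those eight women, and "The midwife and the principal researcher will adopt administrative roles and monitor the WeChat groups".
- **Blinding:** on the midwife's position, "It is not possible for the midwife delivering the intervention to be blinded to the pregnant women in the intervention groups or the usual antenatal" (the sentence closes by naming the comparator arm). The principal researcher is described as blinded only for the data analysis.

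**The concern.** Sealed opaque envelopes hide the content of the next envelope from someone who can only look at it. They do not hide it from someone who can count. With one fixed block size, the count of past allocations fixes the end of every block. Once eight women in a block have gone to one arm, all remaining envelopes in that block belong to the other arm. Here the count has a visible marker, because eight intervention women also make up one training group.

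If a person who influences enrolment knows the next arm, women thought likely to attend can be brought forward, held back or encouraged differently. Two kinds of result are exposed:

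- the two adherence progression criteria, each set at 18 of 24 intervention women;
- the between-arm comparison of urinary incontinence outcomes, which the analysis section uses to look for promise and to plan the definitive trial.

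The problem is separate from who generates the list. Handing the list to an independent person would leave a fixed, countable block in place.

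**Working it through.** **Inputs.** N = 48 and 24 per arm (Sample size); block of 16 (Recruitment section); training groups of eight (Interventions). The article makes no formal sample size calculation, so there is no power figure to reproduce.

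**Structure.** 48/16 = 3 complete blocks. Under 1:1 allocation within blocks, 16/2 = 8 places per arm per block. 24/8 = 3 training groups. One block supplies exactly one group, with none left over. This follows by arithmetic; the article does not say it in words.

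**Certain assignments.** Take an observer who knows the block size and all past allocations. For a block of 2m with m per arm, the probability that at least the last k assignments are certain is 2·C(2m−k, m)/C(2m, m). With m = 8, C(16, 8) = 12,870:

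- k = 1: 2 × 6,435/12,870 = 100%
- k = 2: 2 × 3,003/12,870 = 46.7%
- k = 3: 2 × 1,287/12,870 = 20.0%
- k = 4: 2 × 495/12,870 = 7.7%

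Summed over all k, the mean is 2m/(m+1) = 16/9 = 1.78 per block. Over three blocks it is 5.33 of 48, or 11.1%. By symmetry half of these, 5.33/2 = 2.67, are intervention places.

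**Best guessing.** If the observer always guesses the arm with more places left, the expected number correct per block is m + (2^(2m)/C(2m, m) − 1)/2 = 8 + (65,536/12,870 − 1)/2 = 10.05 of 16, or 62.8%. Over three blocks this is 30.1 of 48, against 24 by chance.

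**Alternatives, per 48 women.** Random-size figures are simulated, for an observer who knows the set of sizes but not their order. The others are exact.

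| Scheme | Certain | Best-guess rate | First eight intervention women not reached by 16th woman |
|---|---|---|---|
| Fixed 16 (plan) | 5.3 | 62.8% | 0% |
| Random 8/12/16/20 | about 0.4 | about 62.5% | about 20% |
| Random 8/12/16 | about 0.7 | about 63.5% | about 16% |
| One 24:24 list | 1.9 | about 58% | 38% |

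For the single list, certain assignments are 48/25 = 1.92. The 38% is (1 − P)/2, where P = C(24, 8)²/C(48, 16) = 0.24 is the chance of exactly eight intervention women among the first 16.

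A fixed block of 4 would be worse than the plan, with 33% certain and 70.8% guessable. The weakness is therefore not that 16 is too small, but that the size is single, fixed and equal to twice the visible group size.

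**The case against.** The case against is substantial, and much of it stands.

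- **Who could use the count.** The principal researcher, who obtains consent, already generates the list, so counting tells that person nothing new under the plan as written. The midwife sees a woman for baseline data and the envelope only after consent is signed. Envelopes go out in sequence, and consent must fall before 24 weeks, which limits room to shift women. This stands, and it is why the opening is modest.
- **What is inferred.** A reader might conclude that staff can watch each WeChat group fill and so work out the end of each block. The article does not say when a group is created, whether women join one at a time, or that each group is drawn from one block. It also does not say that the midwife knows the block size. What it does say is that she offers the envelopes and books the intervention women, so she sees the allocations.
- **Retention.** A reader might infer that the retention criteria are biased too. They are pooled over both arms (40/48, 38/48, 36/48), so moving enrolled women between arms leaves them unchanged.
- **Size of bias.** A reader might attach a bias to the incontinence comparison. If every guess shifted the enrolled woman by 0.25 SD on a prognostic trait, the between-arm bias would be 0.25 × (30.14 − 17.86)/24 = 0.13 SD. Nothing in the article supports the 0.25 SD or its use at every assignment. The Discussion also says that the data will not be used to judge effectiveness.
- **Convenience.** Matching the block to the group guarantees eight intervention women by the 16th enrolment. That is a genuine practical advantage, and any change gives some of it up.

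What survives is that the block size is fixed, single and not stated to be withheld, and that correcting this costs very little.

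**Conclusion.** The concern holds as a modest weakness that is cheap to correct. To an observer who knows the block size and the past allocations, 5.3 of 48 assignments (11%) are certain, and 62.8% can be guessed. Two assumptions carry this: allocation is 8:8 within each block, which follows from 24 per arm, and someone involved in enrolment knows or infers the size of 16. For the principal researcher the second is certain, but that person also holds the list. For the midwife it is an inference.

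The consequence is confined mainly to the two 18/24 adherence criteria, where one woman is 1/24 or 4.2 percentage points, and to the exploratory between-arm comparison. The documents do not support a claim that selection will occur, a numerical bias, or any effect on the pooled retention criteria.

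**What to change.** In the randomization section, replace the fixed size with a statement to this effect: the list is produced by computer in permuted blocks whose sizes are drawn at random (for example from 8, 12, 16 and 20); sizes and sequence are withheld until recruitment ends from the midwife who offers the envelopes and from the principal researcher who obtains consent; each training group is formed from the next eight women allocated to the intervention, whichever block they come from. Remove the block size from any document that recruiting staff use, and report it with the results.

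For the principal researcher this works only if someone else generates and holds the list, so the two changes belong together.

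**What it achieves.** Certain assignments fall from 5.3 to under 1 of 48. The best-guess rate hardly moves, at about 62–64%, so the gain lies in removing certainty rather than guessing.

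**What it costs.** A new list, a few sentences, and someone outside enrolment to hold the list. The first group of eight is not complete by the 16th woman in roughly 16–20% of sequences. The arms may be slightly unequal at 48, so the adherence criteria should be applied as 75% of the women actually allocated.

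A single 24:24 list without inner blocks is an option. It lowers the guess rate to about 58%, but 1.9 assignments stay certain, and the first eight are not reached by the 16th woman in 38% of sequences. With sessions run in groups of eight, that is a poorer trade.

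The Trial status section says that recruitment had not begun at submission. If it has begun since, the unused part of the list can be regenerated, or the predictability reported as a limitation.
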